### Statistical approach and power

The primary outcomes for the study are time-to-event outcomes, such as time to death, a renal event or a clinical cardiovascular event. Some of these events will be known exactly on a continuum and could be right-censored. Exact dates for the occurrence of some of the events, however, may only be known to occur within a specific time interval t_k_, k = 1, 2, 3, 4, 5 (t_1 _= 0-3 months, t_2 _= 3-12 months, t_3 _= 12-24 months, t_4 _= 24-36 months, t_5 _= 36-48 months). The endpoints of these five time intervals correspond to the planned in-person study visits. Therefore, the statistical analyses in these situations will invoke continuous time-to-event models that account for right-censored and interval-censored data.

The hazard function for a continuous time-to-event outcome is of the form

$$\lambda_{\text{ijk}}(\text{t};{\text{x}}_{\text{ijk}})=\lambda_{0}(\text{t})\exp({\text{x}}_{\text{ijk}}\beta )$$

where

(a) λ_ijk_(t; x_ij_) is the hazard function at time t with covariate vector x_ijk _for the k^th ^member of the j^th ^matched set within the i^th ^site, j = 1, 2,...,n_i_, and k = 0 (non-AKI), 1 (AKI),

(b) λ_0_(t) is the baseline hazard function,

(c) β is an unknown parameter vector, and

(d) x_ijk _is a vector of regressors of interest.

The regressors that will appear in x_ijk _for the primary statistical analyses are as follows using as examples different variables: binary indicator variables at month 0 for non-AKI/AKI status, CKD status, gender, Hispanic ethnicity, cardiovascular disease status, diabetes status and sepsis status; ordinal variables at month 0 for racial group (0 = white/European, 1 = Black/African American, 3 = Asian/Pacific Islander, 4 = Native American, 5 = Other/Admixed), eGFR (0 = 15 to 29, 1 = 30 to 44, 2 = 45 to 59, 3 = 60 to 89, 4 = 90-150) and albumin-to-creatinine ratio (0 = <0.15, 1 = 0.15 to 0.5, 2 = >0.5 to 1.0, 3 = >1.0 to 3.0, and 4 = >3.0), age (0 = 1 to 17, 1 = 18 to 39, 2 = 40 to 49, 3 = 50 to 59, 4 = 60 to 69, 5 = 70 to 79, 6 = 80 to 89).

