The hazard model described above, however, is not the final form of the hazard model that will be applied in this study. Instead, the hazard model needs to account for (1) the dependency between an AKI subject and a non-AKI subject within a matched pair and (2) informative censoring. The occurrence of some of the renal and cardiovascular events may not be independent of the censoring event of death. For example, individuals who are censored because of death may have been at higher risk for renal and cardiovascular events. Therefore, a bivariate hazard function for the simultaneous modeling of the renal (or cardiovascular) event and death is invoked [54,55]. Let (T_ijk_, D_ijk_) denote the continuous time of a renal or cardiovascular event and the time of death, respectively, for the k^th ^member of the j^th ^pair within the i^th ^site, j = 1, 2,...,n_i_, and k = 0 (non-AKI), 1 (AKI). The bivariate hazard model is

$$\lambda_{\text{T,ijk}}(\text{t};{\text{x}}_{\text{ijk}})=\lambda_{\text{T0}}(\text{t})\exp({\text{x}}_{\text{ijk}}\beta_{\text{Ti}}+{\text{e}}_{\text{Tij}})\;\text{and }\lambda_{\text{D,ijk}}(\text{d};{\text{x}}_{\text{ijk}})=\lambda_{\text{D0}}(\text{d})\exp({\text{x}}_{\text{ijk}}\beta_{\text{Di}}+{\text{e}}_{\text{Dij}})$$

where the [e_Tij _e_Dij_]'s are independent and identically distributed according to a bivariate normal distribution with null mean vector and positive-definite variance matrix. The covariance between e_Tij _and e_Dij _represents the magnitude of the relationship between the occurrence of the renal (or cardiovascular) event and the censoring event of death. An estimated value of the covariance near zero indicates non-informative censoring, whereas an estimated value of the covariance distant from zero indicates informative censoring.

The sample size for the study is (1) 550 adult AKI subjects and 550 matched adult non-AKI subjects and (2) 50 pediatric AKI subjects and 50 pediatric non-AKI subjects, at the 3-month visit. For a two-sided, 0.05 significance level test of the relative risk equaling 1.0, the sample size of 1,200 yields greater than 80% statistical power, while allowing for a 15% withdrawal rate, for detecting a relative risk between 1.35 (when the event rate for AKI subjects is 30%) and 1.90 (when the event rate for AKI subjects is 10%).

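### A covariance distant from zero shows that event and death are associated; it does not by itself show informative censoring, as the protocol article says

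*Protocol article*

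**What the plan says.** All of this stands in the protocol article, section Statistical approach and power.

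- Because censoring by death may be informative, "a bivariate hazard function for the simultaneous modeling of the renal (or cardiovascular) event and death is invoked". T and D "denote the continuous time of a renal or cardiovascular event and the time of death, respectively".
- Each hazard is a baseline hazard times the exponential of the same covariate vector x (with its own coefficients) plus a random effect. The random effects carry the indices of site and matched set, not of person, and are "independent and identically distributed according to a bivariate normal distribution with null mean vector and positive-definite variance matrix".
- The regressors, given as examples, are all month-0 values, starting with "binary indicator variables at month 0 for non-AKI/AKI status, CKD status, gender, Hispanic ethnicity, cardiovascular disease status, diabetes status and sepsis status". None is an event during follow-up, and T does not appear in the hazard for D.
- The covariance of the two random effects "represents the magnitude of the relationship between the occurrence of the renal (or cardiovascular) event and the censoring event of death". A value near zero is read as non-informative censoring, and "an estimated value of the covariance distant from zero indicates informative censoring".
- Death is an outcome in its own right: "The primary outcomes for the study are time-to-event outcomes, such as time to death, a renal event or a clinical cardiovascular event".

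**The concern.** Death censors the event informatively if those who die event-free had a different event risk from those who stay under observation. The article's own example has this meaning. A death after the event is another matter: the event has already been seen and nothing is censored.

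The printed model cannot tell the two apart. Its death hazard is the same before and after an infarction, a heart failure admission or progression of CKD. If such an event raises mortality, event and death times are associated, and the covariance is the only parameter that can express this. It then moves away from zero even when deaths before the event are unrelated to event risk. Where shared risk does exist, the covariance is too large.

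Handling informative censoring is one of two stated reasons for the final model, and this sentence is the only guidance on how to judge it. A report that follows it could announce informative censoring where there is none, or overstate it.

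**Working it through.** **1. The plan's own figure.** The only numerical claim nearby is power above 80% after 15% withdrawal. With n = 600 × 0.85 = 510 per group and a non-AKI rate equal to the AKI rate divided by the relative risk:

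z = [d√n − 1.96√(2p̄(1−p̄))] / √(p₁(1−p₁)+p₂(1−p₂))

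- RR 1.35: p₁ = 0.30, p₂ = 0.2222, z = 0.871, power 80.8%.
- RR 1.90: p₁ = 0.10, p₂ = 0.0526, z = 0.893, power 81.4%.

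The figure reproduces, and the present point does not touch it.

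**2. The structure.** Write a for the hazard of the event, b for the hazard of death before it and c for the hazard of death after it. Whether censoring of the event by death is informative depends on a and b only. The printed model forces c = b, given x and the pair effect. If in truth c = r × b with r > 1, the excess deaths after events have no place except in the random effects.

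**3. Simulation inputs.** From the article: matched pairs, up to four years of follow-up, and the two printed hazards. Assumed, because the article gives no figures: event hazards of 0.063 (non-AKI) and 0.089 (AKI) per year; pre-event death hazard of 0.04 per year in non-AKI and 1.35 times that in AKI; r from 1 to 5. The event and death pair effects were independent, so the true covariance is 0. The printed model was fitted by maximum likelihood with piecewise-constant baselines, with and without a time-dependent prior-event indicator in the death hazard.

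**4. Estimated covariance, 15,000 pairs (truth 0).**

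| True pair-effect SD | r | Printed model | With prior-event indicator |
|---|---|---|---|
| 0 | 1 | 0.01 | 0.02 |
| 0 | 2 | 0.16 | 0.00 |
| 0 | 3 | 0.31 | 0.02 |
| 0 | 5 | 0.46 | 0.00 |
| 0.5 | 1 | −0.02 | −0.05 |
| 0.5 | 2 | 0.25 | −0.01 |
| 0.5 | 3 | 0.38 | −0.02 |

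With no pair effects, the indicator also recovered the log death ratio: 0.69, 1.08 and 1.59 against true values of 0.69, 1.10 and 1.61.

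**5. Study size.** At 510 pairs with pair-effect SD 0.5 (32 or 33 runs per setting, so rough), the printed model gave a mean covariance of 0.00, 0.24, 0.39 and 0.61 for r = 1, 2, 3 and 5. A likelihood-ratio test at 5% called it non-zero in 3%, 55%, 100% and 100% of runs; with the indicator, in 3%, 0%, 0% and 6%. When deaths after the event were left out of D, the median covariance lay between −0.04 and 0.03, which identifies those deaths as the source. Separate fits at 550 pairs with true covariance 0 gave 0.17 for r = 2 and 0.23 to 0.31 for r = 3, and 0.36 for r = 3 with pair-effect SD 0.5. The size varies between these runs; the direction does not.

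**6. Effect on the AKI hazard ratio for the event.** AKI log hazard ratios from the same 15,000-pair data, printed model minus model with indicator:

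- SD 0: 0.393 − 0.381 = 0.012 (r = 2); 0.364 − 0.340 = 0.024 (r = 3); 0.419 − 0.375 = 0.044 (r = 5).
- SD 0.5: 0.383 − 0.375 = 0.008 (r = 2); 0.342 − 0.320 = 0.022 (r = 3).

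The largest gives exp(0.044) = 1.045. At 550 pairs the ratios without and with the indicator were 1.42 and 1.40, and 1.40 and 1.37.

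**7. Effect of the indicator on the AKI coefficient for death.** In the 15,000-pair fit with r = 3 and no pair effects, the AKI log hazard ratio for death fell from 0.385 to 0.316, that is from exp(0.385) = 1.47 to exp(0.316) = 1.37. Part of the AKI effect on death runs through the event, and the indicator removes that part.

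**The case against.** **No decision hangs on the covariance.** The article names no threshold, test or action, and the joint model is used whatever the value. This stands. The rejection percentages above use a test that the article does not specify and only illustrate how far the estimate moves.

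**Shared risk is expected.** The article anticipates that those who die were at higher event risk. If so, the reading is right in kind and only the size is inflated. This stands too. A reader might infer that a false reading is the most likely case, but the documents give no effect of the event on death that would support this. The Discussion calls CKD and its severity strong predictors of adverse outcomes. That makes some effect plausible without sizing it.

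**The article is condensed.** The likelihood is not written out, the regressors are examples, and the problem disappears if deaths after the event do not enter D. This stands in part. Yet the equation and the sentence on its meaning are both printed, D is defined as the time of death, and death is itself a primary outcome. Following D past T is the natural reading.

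**The AKI effect is hardly touched.** A reader might infer that the model distorts the AKI hazard ratio for the event. For the pair-level model that the article prints, step 6 does not support this.

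**The indicator is not free.** A reader might infer that it belongs in the primary death model. It does not, because the AKI coefficient for death would no longer be a total effect (step 7). In a check where AKI acted on death only through the event, the total rate ratio was 1.05 and the conditional one 0.99. The article also says that some event dates are known only to within a visit interval, so the indicator would switch on at an approximate time.

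**Conclusion.** The point holds as a fault in the stated interpretation of the covariance. As written, the sentence is wrong: a covariance distant from zero shows that event and death are associated, and the printed model cannot say whether this comes from shared risk or from the effect of the event on later death. With a true covariance of 0, the estimate at 15,000 pairs was 0.16 to 0.46 for death ratios of 2 to 5 without pair effects, and about 0 for a ratio of 1. Where shared risk is real, the covariance is inflated by the same route; the amount was not quantified here.

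This rests on two assumptions: that a non-fatal event raises later mortality, by a ratio that the documents do not give, and that D is followed beyond T. The consequence for the AKI hazard ratio for the event is small, at most about 4.5% in these fits. The sentence is worth correcting, but the primary model need not be replaced.

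**What to change.** Replace the sentence with wording such as:

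> A non-zero covariance shows an association between the event and death. It may reflect shared risk, an effect of the event on later death, or both. Informative censoring will be judged from a supporting fit that adds a time-dependent indicator of a prior event to the death hazard.

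An alternative supporting fit ends the death follow-up used for the covariance at the event. Keep the model without the indicator for the total effect of AKI on death, and state that the AKI coefficient for death in the supporting fit is conditional on the event.

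The cost is one additional fit and no new data. The covariance becomes less precise: in 30 runs of 550 pairs with true covariance 0.34, its standard deviation was 0.17 with the indicator and 0.12 without, and a true covariance of that size was detected in only about half the runs. A value near zero in the supporting fit is therefore weak evidence of non-informative censoring. Where event dates are interval-censored, the event time used for the indicator is approximate, and an event may be missed if death comes before the next visit. The plan should say how such dates are assigned.

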## Discussion

Despite the emerging clinical and public health importance of AKI, studies to date have traditionally focused on characterizing its short-term consequences. Recent attempts to extend focus on longer-term outcomes have primarily involved the retrospective study of administrative databases in different population and clinical settings [9-14]. While these studies have reported a link between AKI and increased risk for either advanced CKD,[9,14] ESRD,[10-13] and all-cause death,[9-12,56-59] there have been several important limitations. Specifically, all published studies were retrospective in nature. Many did not use observed changes in serum creatinine to define AKI or rigorously quantify baseline renal function or but rather relied on administrative diagnostic codes for defining "AKI" and determining presence or absence of baseline CKD and potential confounders. Most studies included only a relatively small number of outcomes. Importantly, none of the studies collected specimens to measure biomarkers both during the AKI admission and after hospital discharge. The ASSESS-AKI study will address many of these limitations by establishing a prospective, matched parallel cohort of persons (including children) with and without AKI based on serum creatinine-based criteria measured in a standardized fashion, serial collection of blood and urine for evaluating of diagnostic and prognostic markers in AKI, and systematic follow-up for changes in renal function and multiple clinical and patient-centered outcomes.

One of the key challenges of existing studies relates to defining "baseline" kidney function for determination whether an episode of AKI has occurred and the severity of AKI [60,61]. A recent examination of this issue revealed that the use of imputed or commonly used surrogate estimates of baseline function can result in substantial misclassification of AKI and hinder adequate study of its associated outcomes [62]. Enrollment into ASSESS-AKI requires a pre-admission serum creatinine performed using an IDMS-traceable assay using a time frame recent enough to the index hospitalization that is likely to represent steady-state renal function and will substantially reduce the misclassification of the main exposure (i.e., occurrence of AKI) and of a key confounder (pre-admission CKD status) for enrolled participants, but it also creates barriers to participant recruitment. Many hospitalized patients who experience or are at risk for AKI may not have serum creatinine values available before the AKI episode, available values may not be performed using an IDMS-traceable assay, available values may be outside of our pre-specified time window (7 to 365 days before the index hospitalization), or values obtained during the eligible time window may not actually reflect steady-state renal function. All studies of AKI are affected by this challenge given that currently available consensus definitions of AKI are based on the magnitude of change of serum creatinine concentration. ASSESS-AKI will have strong internal validity given that both participants with and without AKI will have a consistently measured baseline measure of renal function that will serve as an anchor for assessment of longitudinal changes in kidney function.

As patients who suffer from AKI also tend to systematically differ from those without AKI on relevant demographic and clinical characteristics, accurate assessment of these variables is paramount to delineating the risk attributable to AKI for poor outcomes. Toward that end, existing studies based on their retrospective design and limited data quality have been susceptible to notable residual confounding and biases that limit the ability to delineate the independent contribution of AKI, especially less severe episodes, on adverse clinical outcomes. In particular, the use of administrative codes to capture the primary exposure (AKI) and critically important modifiers such as underlying CKD can lead to misclassification bias reflected in a substantial exaggeration or underestimation of the effect observed. Most studies also did not control for the presence and severity of CKD before the AKI episode, which is problematic given that CKD and CKD severity are both potent predictors of experiencing AKI as well as CKD progression, ESRD and other adverse outcomes. In addition to using standardized measurements of serum creatinine in detailing both AKI and CKD, ASSESS-AKI will also implement a 1:1 AKI:non-AKI participant matching algorithm along with advanced analytic methods that should help to mitigate major confounding for evaluating the independent impact of AKI on targeted outcomes of interest during long-term follow-up.

Current efforts to develop and validate diagnostic biomarkers that can define and predict both AKI and CKD progression based on absolute levels rather than on changes from baseline--as is necessary when utilizing serum creatinine concentrations--may mitigate the challenges of requiring a standard definition. One of the major goals of ASSESS-AKI is to evaluate the incremental utility of blood and urine biomarkers to refine the diagnosis and prognosis of AKI above current definitions using a prospective serial biospecimen collection protocol; standardized collection, processing, storage and testing methodology; and a diverse set of clinical settings and patients. Most of the recently discovered putative biomarkers of AKI are known to demonstrate time-dependent fluctuations around the time of AKI [18]. Some biomarkers are most elevated within a few hours after a known insult such as cardiac surgery (e.g., NGAL, L-FABP), while other prominent biomarkers have a delay in their expression, with peak values occurring 24-48 hours after the time of presumed injury (e.g., IL-18, KIM-1) [18]. We anticipate that the timing of the presumed renal insult will vary across the three Clinical Research Center populations that comprise ASSESS-AKI. The TRIBE-AKI cohort will, in general, experience injury occurring during or after the time of cardiopulmonary bypass; the VALID cohort may have multiple episodes of injury in the setting of critical illness, and the Kaiser Permanente cohort will have variation in timing of injury depending on the clinical setting (e.g., medical or surgical wards, oncology or cardiology service) within a general hospitalized population. Thus, our approach is tailored to promote generalizability and pragmatism for biospecimen collection, as both blood and urine will be collected on the day of or as soon as possible after the identification of clinical AKI based on serum creatinine concentration change. Based on this approach, it remains questionable whether biomarkers of current interest will be at or near their peak concentration. However, if biomarkers of AKI are to be widely used by practicing physicians, they are most likely to be initially used when there is evidence of AKI by standard diagnostic criteria to improve the diagnosis and/or prognosis of AKI. Therefore, the results from ASSESS-AKI should be broadly generalizable to clinical practice.

In addition to the challenges mentioned above, characterizing the type of AKI, which could influence short- and long-term outcomes, has been relatively understudied in epidemiologic studies of AKI. Both AKIN and RIFLE consensus criteria do not encourage discrimination of the type of AKI (i.e., ATN, pre-renal azotemia, other), implying that the etiology and type of AKI do not affect subsequent outcomes after accounting for the magnitude of change in serum creatinine concentration and/or urine output. However, ASSESS-AKI will prospectively evaluate the contribution of type of AKI on long-term clinical outcomes -above and beyond conventional measures of AKI severity. We believe that attempting to differentiate AKI "phenotype" (i.e., ATN vs. pre-renal azotemia vs. other) is important to address this knowledge gap. We also recognize that there currently exists no "gold standard" method to distinguish between phenotypes and that the same patient could have multiple contributing etiologies for AKI. Thus, we will implement several strategies, including targeted enrollment of more severe AKI based on greater change in serum creatinine concentration and/or longer duration of serum creatinine elevation that is more likely to represent ATN; urine analysis and microscopy at the time of AKI for identification of urine sediment consistent with ATN (e.g., granular casts); and standardized adjudication of cases via consultation notes, discharge summaries, and other clinical variables. Overall, the ASSESS-AKI study will provide one of the most comprehensive efforts to characterize AKI phenotype and whether it independently alters the risk of long-term clinical outcomes.

While ASSESS-AKI has numerous strengths, it also has several limitations. The cohort will be enriched with patients suffering AKI in common at-risk settings such as surrounding cardiac surgery or within the ICU as well as in more general hospitalized settings, but we will have limited power to examine whether the clinical setting modifies the association between AKI and clinical outcomes. The inclusion of children expands the age range being evaluated but is only applicable to those requiring cardiopulmonary bypass. The relatively small number of children targeted for enrollment means we will be able to detect only large effect sizes. The multi-center cohort includes various U.S. and Canadian sites and health care delivery systems, but the results may not be generalizable to all practice settings and populations. Despite various design and analytic approaches as well as standardized data collection and quality control efforts, as an observational study, we cannot rule out the impact of residual confounding and bias. However, since a randomized comparison is not possible, our prospective cohort design and systematic follow-up will provide a rigorous assessment among eligible participants. There are ongoing plans to address some of these limitations by augmenting ASSESS-AKI with possible ancillary studies (e.g., recruitment of a larger number of pediatric patients).

